##### Primary Outcome: Cognitive Performances

The primary outcome of the study will be cognitive performances. Participants will be tested for general cognitive functioning using a remote version of the Montreal Cognitive Assessment (MoCA) (24). Also, three main components of cognition will be assessed with a comprehensive neuropsychological evaluation, from which composite z-scores will be computed: executive functions, processing speed and episodic memory. The neuropsychological assessment will include the following tests that will be administered in a predetermined order: Rey auditory verbal learning test, Digit Span, oral Trail Making Test (25), Phonological and Semantic Fluency from the D-KEFS battery (26), and Similarities subtest from the WAIS-IV (27). The neuropsychological assessment, including the MoCA, will be performed via videoconference (Zoom). All tests have been validated for remote administration and have previously been used in large participant cohorts (28). Importantly, these tests are validated and normed for an older adult population (17, 21, 29). The similarities subtest will only be completed at baseline to obtain a measure of crystallized intelligence; its completion will be optional and performed according to participant's fatigue. Participants will also realize a computerized or tablet-based cognitive assessment (30). The three computerized cognitive tasks include a dual-task (30), Stroop task, and N-back. Participants will complete trained and transfer versions (same tasks but with different stimuli) that will be presented in a counterbalanced order between participants, via a latin-square procedure. Comparing trained and transfer tasks allows to quantify participants' ability to transfer cognitive training effects to novel tasks. Subcomponents of each task allow dissociating different attentional control mechanisms from mere cognitive speed. Importantly, the tasks record response time in milliseconds, which reduces the likelihood of ceiling effects. These tasks also tend to be more sensitive to training effects. Finally, computer equipment (i.e., computer or tablet) used by participants for the computerized tasks will be documented. Participants will be asked to use the same computer equipment for the four testing periods (including the 12-month follow up).

##### Secondary Outcome: Physical Functions

Physical functions will be assessed remotely by videoconference. First, balance will be assessed with a one-leg balance test (i.e., stay on one leg as long as possible for a maximum of 60 s; recorded twice for both legs). Lower limb muscle strength will be evaluated with the Five-Time-Sit-to-Stand test (i.e., five consecutive sit-to-stand movements performed as fast as possible without using arms as leverage). The 4-meter walk test and the Timed Up-and-Go (TUG) performed at spontaneous and fast speeds will be used to assess mobility. During the 4-meter walking test, participants' walking speed will be measured in a straight line over 4 meters. During the TUG, participants will be timed for the following sequence: getting up from a chair, walking 3 meters, turning around, and sitting back in the chair. These four tests are commonly used in a clinical setting and have demonstrated their associations with global cognition and specific cognitive domains such as processing speed and executive functions (31). During the physical function session, participants will be first questioned about their history of musculoskeletal and sensory conditions to ensure that they can safely execute the tests. Prior to the physical function assessment, participants will receive by email with a detailed description of each test with its set-up and demonstration videos. Then, at the beginning of the session, the testing set-up will be verified by the research assistant or kinesiologist, to ensure there is sufficient space to perform the tests, as well as a sufficient accuracy for both 4 and 3-m of the walking and TUG tracks measures. During the testing, adequate visual feedback will always be maintained to ensure participant's security and reliability of the measures. Finally, to complete the physical function assessment, the Matthews questionnaire will be used to predict participants' cardiorespiratory fitness (i.e., VO2_max_), which is based on sex, age, anthropometric data, and self-reported physical activity level (32).

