## Abstract

**Introduction:** During the COVID-19 pandemic, confinement measures are likely to produce collateral damage to health (stress, confusion, anxiety), especially in frail individuals and those living with cardiovascular disease (CVD). In cardiac patients in particular, these measures dramatically increase the level of physical inactivity and sedentary lifestyle, which can decrease cardiorespiratory capacity and increase the risk of acute events, rehospitalization, and depressive syndromes. Maintaining a minimum level of physical activity and cognitive stimulation during the COVID-19 crisis is essential for cardiac patients. This study is designed to document the effects of 6 months of home-based physical exercise alone or combined with cognitive training on cognitive and physical functions in patients with CVD over 50 years old.

**Methods and Analysis:** 122 patients (>50 years old) with stable CVD and no contraindication to perform physical exercise training will be recruited and randomly assigned to one of the 2 following arms: (1) Home-based physical exercise alone, (2) Home-based physical exercise combined with cognitive training. The intervention lasts 6 months, with remote assessments performed prior to, mid and post-training. A follow-up 6 months after the end of the intervention (12 month) is also proposed. The primary outcome is cognition, including general functioning (Montreal Cognitive Assessment (MoCA) score), as well as performances on measures of executive functions, processing speed, and episodic memory. The secondary outcome is physical performance, including balance, gait and mobility, leg muscle strength and estimated cardiorespiratory fitness. Tertiary outcomes include mood, anxiety, and health-related quality of life as assessed by self-reported online questionnaires.

**Discussion:** With the COVID-19 crisis, there is a critical need for remote exercise and cognitive training, and to further investigate this topic, in particular for cardiac patients. The present context can be viewed as an opportunity to perform a major shift from center-based programs to home-based physical exercise. This is especially important to reach out to older adults living in remote areas, where access to such interventions is limited.

**ClinicalTrials.gov:** [https://clinicaltrials.gov/ct2/show/NCT04661189], NCT04661189.

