### Data Analysis

#### Sample Size Calculation

The team of biostatisticians from the Montreal Health Innovations Coordinating Centre (MHICC) performed the sample size calculation on the primary outcome, i.e., the differential effect of physical exercise training alone vs. the combined physical and cognitive training on cognitive performance (executive functions). The calculation was based on existing values available in the literature for physical exercise training alone, as well as on different plausible effect sizes for the combined physical and cognitive training (no existing values in the literature for this group), and on clinically relevant effect sizes. The calculation revealed that a sample size of 49 subjects in each group will have 80% power to detect a difference in means of−0.186 (difference between physical training alone mean of 0.239 and combined training mean of 0.425, for an effect size of 0.624), assuming that the common standard deviation is 0.325 (slightly larger than in a traditional context because of the home-based administration of neuropsychological tests) using a two-group *t*-test (0.050 two-sided significance level). As we expect a 20% attrition rate based on our previous exercise studies, we will thus recruit 61 participants per intervention arm, for a total of 122 patients with CVD. Participants will be randomized in one of the 2 arms: home-based physical training alone or combined physical and cognitive home-based training. A biostatistician from the MHICC generated the randomization sequence.

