#### Statistical Analysis

The variables in the study will be presented using descriptive statistics. The mean, standard deviation, median, minimum, Q1, Q3 and maximum will be presented for continuous variables. The number and percentage will be presented for nominal/ordinal variables. The assumptions of the statistical tests will be examined, and data transformation or non-parametric analyses may be used as appropriate. SPSS and SAS software version 9.4 or higher will be used to conduct the analyses.

Mean changes in cognitive performance from baseline will be analyzed using a repeated measures analysis of covariance (ANCOVA) model, adjusted for age, sex, education, including the effects of the intervention as between-subject variable (physical exercise alone or combined with cognitive training) and time as within-subject variable (pre at baseline, mid at 3 months, post-intervention at 6 months). Observation of a statistically significant difference in the primary outcome between pre- and post-intervention timepoints will be considered as the evidence of the intervention's efficacy (i.e., primary hypothesis). The interaction between intervention arms (i.e., physical exercise alone or combined training) and performance changes from pre to post-intervention will address the added value of cognitive training compared to physical exercise alone (i.e., secondary hypothesis). Secondary and exploratory outcomes will be analyzed as the primary outcome.

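### The one-leg balance test is capped at 60 s but analysed as an uncensored mean change; if a material share of patients reach the cap, the balance effect shrinks towards zero and power falls

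*Protocol article*

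**What the plan says.** All places are in the protocol article.

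- **Outcome.** The Abstract states: "The secondary outcome is physical performance, including balance, gait and mobility, leg muscle strength and estimated cardiorespiratory fitness". Under Secondary Outcome: Physical Functions, balance is measured by one test, performed as "stay on one leg as long as possible for a maximum of 60 s; recorded twice for both legs". No upper limit is given for the sit-to-stand, 4-meter walk or Timed Up-and-Go tests.
- **Model.** Statistical Analysis says: "Mean changes in cognitive performance from baseline will be analyzed using a repeated measures analysis of covariance (ANCOVA) model, adjusted for age, sex, education". Baseline, 3 months and 6 months are the levels of time. The pre-to-post difference serves the first hypothesis and the arm-by-time interaction the second.
- **Extension to balance.** The same section adds: "Secondary and exploratory outcomes will be analyzed as the primary outcome".
- **Fallback.** It also says: "The assumptions of the statistical tests will be examined, and data transformation or non-parametric analyses may be used as appropriate".
- **Ceilings elsewhere.** For the computerized cognitive tasks the article notes that "the tasks record response time in milliseconds, which reduces the likelihood of ceiling effects". It makes no such remark for balance.

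**The concern.** A score stopped at 60 s is right-censored: 60 means at least 60. The mean-change model reads it as exactly 60. A patient at the cap at baseline can only stay or fall, and a patient who moves from 50 s to a true 90 s is credited with 10 s.

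Both hypotheses cover physical function, and the exercise videos offered to both arms include balance exercises. If exercise works, more patients reach 60 s at follow-up, so the loss grows with success. A null balance result could then reflect the cap and not the intervention, and the planned output would not show which. The article fixes the model for this outcome in words, so the point concerns a stated rule and not a missing detail.

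**Working it through.** **1. The plan's own figure.** The sample size rests on executive functions: difference 0.425 − 0.239 = 0.186, SD 0.325, ratio 0.186/0.325 = 0.572. A two-sided 5% t-test then needs 48.9, so 49 per group (power 80.1%), which agrees with "a sample size of 49 subjects in each group will have 80% power". Attrition gives 49/0.80 = 61.25, stated as 61 per arm. None of this involves balance, so the cap changes neither 49 nor 122. The article states no power for balance.

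**2. Assumed inputs for balance.** The article gives no balance time, SD, expected gain or share at 60 s. Assumed: log seconds normal with SD 0.9 at each visit, pre-post correlation 0.8, true arm effect 0.30 log units, 49 per arm, one recording per visit. The share at the cap at baseline, c, is varied from 5% to 40%. The common gain in both arms, g, is 0 or 0.30.

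**3. Uncapped reference.** SD of log change = 0.9 × √(2 × (1 − 0.8)) = 0.569. Standardised effect = 0.30/0.569 = 0.527. The t-test at 49 per arm has 73% power; the simulations gave 74–75%.

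**4. Expected arm contrast under the cap.** For a normal variable cut off at a cap k SDs above its mean, the mean falls by SD × L(k), where L(k) = φ(k) − k(1 − Φ(k)). Baseline terms cancel between randomised arms, so

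observed effect = 0.30 − 0.9 × [L(k1) − L(k0)], with k0 = z(1−c) − g/0.9 and k1 = z(1−c) − (g + 0.30)/0.9.

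Example, c = 40%, z = 0.253:
- g = 0: k0 = 0.253, k1 = −0.080; L = 0.2850 and 0.4402; effect = 0.30 − 0.9 × 0.1552 = 0.160.
- g = 0.30: k0 = −0.080, k1 = −0.413; L = 0.4402 and 0.6392; effect = 0.30 − 0.9 × 0.1990 = 0.121.

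Power is from simulation of the t-test on log change.

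| At cap at baseline | Effect, g = 0 | Power | Effect, g = 0.30 | Power |
|---|---|---|---|---|
| 5% | 0.279 (93%) | 72% | 0.262 (87%) | 66% |
| 20% | 0.225 (75%) | 61% | 0.190 (63%) | 48% |
| 30% | 0.192 (64%) | 56% | 0.153 (51%) | 41% |
| 40% | 0.160 (53%) | 50% | 0.121 (40%) | 30% |

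Simulated effects ran from 93% to 54% and from 89% to 41%, within two points of the formula. The powers should be read with similar tolerance. The pre-to-post gain shrinks too: with g = 0.30, the exercise-alone arm shows the same 0.279 to 0.160.

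**5. Does the fallback help?** Any transformation sends every 60 to one value. In a separate simulation on normal scores (difference 0.572 SD of change, correlation 0.6 to 0.8, 10% to 50% capped), a rank test on change fell from about 77% power to 72–44%, or to 62–21% if the exercise-alone arm also gained 0.5 SD of change.

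**6. Does baseline adjustment help?** Partly. In the same simulation, baseline-adjusted ANCOVA fell from 83–88% to 86–56%, or to 81–45%, so it keeps more power than the change score. It does not remove the bias. On the log scale at 20/30/40% capped it estimated 0.212/0.176/0.147 against a true 0.30; these values match a small common gain of 0.1.

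**7. Does a censored model help?** On the log scale, a tobit-type model with the baseline value and a baseline-at-cap indicator estimated 0.29 to 0.30. Its power was 69.5/65.1/61.8%, against 64.5/59.7/54.5% for log ANCOVA, a gain of 5.0/5.4/7.3 points. Its rejection rate under the null was 4.7/6.7/6.5%.

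**The case against.** **The share at 60 s is unknown.** This stands. A low-risk profile is a physician's judgement about exercise risk and says little about standing balance, and the Discussion describes cardiac patients as tending to be sedentary. A reader might infer that the balance effect is understated as a matter of fact. The documents support only a conditional statement, and at 5% capped with no common gain the loss is small.

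**Power claims can be pushed too far.** This also stands. A reader might infer that the trial's stated power is wrong, but that power belongs to executive functions. Setting uncapped log-scale power (78% for log ANCOVA) against capped power in raw seconds (57/50/45%) would also mislead: under these log-normal assumptions, change in raw seconds has only about 52% power without any cap, because of skewness. Only like-for-like log-scale figures should be used.

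**The fallback clause is broader than a simple rank test.** This stands in part. Rank ANCOVA keeps the covariates and comes within about 4 to 11 points of the censored model's power. It still leaves capped patients tied and does not return the size of the lost gains.

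**The simulation is simpler than the trial.** Each visit yields two recordings on both legs. If they are averaged, a patient is fully at the cap only when all four reach 60 s; if the best is taken, the share is higher. This widens the uncertainty about size but not about direction.

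**The capped score is a legitimate endpoint, and handling could be in an analysis plan.** The randomised comparison on it keeps its type I error, and the scoring of the four recordings may properly be left to an analysis plan. But the article itself assigns the mean-change model to this outcome, so the conflict with the cap lies in its own text.

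**Conclusion.** The point holds in conditional form, for one measure within the secondary domain. The cap and the mean-change model are both stated, and together they bias the balance gain and the arm contrast towards zero to the extent that patients reach 60 s. Over an assumed 5% to 40% at the cap at baseline, the arm effect is seen at about 93% to 53% of its true size with no common gain, or about 87% to 40% if both arms improve as the first hypothesis expects. Power of the log-change test falls from about 75% to 72–50%, or to 66–30%. These sizes rest on an assumed log SD, correlation, true effect and one recording per visit; none comes from the article.

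The primary outcome, the sample size and the other physical tests are not touched. Nor is the planned analysis invalid: a positive balance result would stand. The weakness is in how a null balance result could be read.

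**What to change.** In Statistical Analysis, add a short exception for the one-leg balance test:

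1. Keep the planned analysis but include the baseline value as a covariate, so that 3 and 6 months become the response visits for this measure.
2. Prespecify a supportive analysis that treats 60 s as censored: a tobit-type model on log seconds with arm, visit, arm-by-visit, the stated covariates, the baseline value with an indicator for baseline at the cap, and a patient effect for repeated recordings. Check it with a Cox model for time to loss of balance. The Cox model has no information beyond 60 s either; its use is to test dependence on the assumed distribution.
3. Report the proportion reaching 60 s by arm and visit, and state that a null balance result will be read together with it.

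This needs a few sentences, standard software and no new data. The censored model depends on its distributional assumption and can be slightly liberal at this sample size (up to about 7% in simulation), so it is better placed beside the planned analysis than in its stead. The multi-recording version has not itself been simulated. Fixing it before the data are seen avoids a choice of method that would look post hoc.

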##### Exercise Monitoring

Participants will be encouraged to complete a home-based physical exercise using video capsules available via Facebook or Youtube, created by the Centre EPIC of the MHI's team of kinesiologists (20). Aerobic, muscular strengthening, flexibility, and/or balance exercises are proposed in these videos, and do not require any equipment. Each video lasts ~15 min and includes a 5-min warm-up, followed by a 10-min training, and finally by a 2-min cool-down period. Guidelines are provided by kinesiologists to allow participants to adapt the exercise to their physical capacities. Participants will be invited to perform exercise sessions at least 5 times a week. The exercise sessions can be performed at home using the video capsules, or with other video or web-based training programs. Participants can also engage in outdoor activities (e.g., walking or cycling). To track their adherence, the duration, intensity, and nature of the activity of each training session will be reported by the participant in a journal, that they will transmit to their training coach during their weekly follow-up call. The Borg Rating of Perceived Exertion (RPE) graduated from 0 to 10 will be used by participants to assess the intensity of their exercise sessions.

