**Figure 1 F1:**
[figure not shown]
Schedule of enrolment, interventions, and assessments according to SPIRIT guidelines. ^1^Montreal Cognitive Assessment, Trail Making Test, Verbal Fluency Test, Digit Span Test, Similarity Test, Rey Auditory Verbal Learning Test. ^2^One leg balance test, 5-time Sit to Stand test, Timed up and go test, 4-meter walking speed test. ^3^Matthew questionnaire for estimated cardiorespiratory fitness, SF-12, Pittsburgh Sleep Quality Index and Berlin Questionnaire, Short Diet Questionnaire, Stait Trait Anxiety Inventory, Geriatric Depression Scale, Perceived Stress Scale, Perseverative Thinking Questionnaire, Intolerance of Uncertainty Scale, Connor Davidson Resilience Scale 10, Anxiety Sensitivity Index, Social and Community Involvement Questionnaire, Lubben Social Network Scale. The following questionnaires will be completed at baseline only: Medical questionnaire, Q-COVID questionnaire, Physical Activity Scale for the Elderly, Cognitive Reserve Questionnaire, Bem sex-role Inventory.

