Secondly, our participants do not have precise control of the intensity and duration of the exercise sessions (heart rate monitors, pedometers, or other tools). This is only declarative data reported weekly with the kinesiologists. Our study focuses on exercise and cognitive training in CR's phase III and should not be confused with a comprehensive CR program delivered in phase II. Adherence to medication, diet and appropriate teaching about patient's risk factors and CVD are critical aspects of a comprehensive CR program (phase II). Consequently, we will include some patients who have completed a CR program and others who have not benefited from this program. Then, non-exercise prediction of cardiorespiratory fitness with an equation is valid for healthy individuals, but little is known about its reliability in patients with CVD. Moreover, variability was observed in the accuracy between non-exercise prediction equations and the ability of equations to detect changes in cardiorespiratory fitness (46). Therefore, the use of non-exercise prediction equations could lead to a significant error in the estimated change of participants' cardiorespiratory fitness. Finally, sex was not taken into account in recruitment and randomization processes, although sex differences have been reported on cognition (47), as well as in exercise-training effects on cognition in healthy older adults (48). No study to date has documented potential sex-related differences with regards to the effects of exercise, cognitive or combined training on cognition and physical outcomes in older adults with CVD. Given the sex-related differences in cognition, exercise intervention effects and diseases, sex differences are to be expected in the present study.

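### Change in estimated VO2max, a secondary physical-performance outcome, cannot be told apart from change in self-reported activity in the pre/post and dose-response analyses

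*Protocol article*

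**What the plan says.** All references are to the protocol article.

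- **Tier.** Abstract: "The secondary outcome is physical performance, including balance, gait and mobility, leg muscle strength and estimated cardiorespiratory fitness".
- **Construction.** Secondary Outcome: Physical Functions says that "the Matthews questionnaire will be used to predict participants' cardiorespiratory fitness", by a prediction "which is based on sex, age, anthropometric data, and self-reported physical activity level". The other four measures in that section (one-leg balance, five-time sit-to-stand, 4-meter walk, Timed Up-and-Go) are performed under observation by videoconference.
- **Repetition.** The Figure 1 legend puts the instrument among the self-report questionnaires: "Matthew questionnaire for estimated cardiorespiratory fitness, SF-12, Pittsburgh Sleep Quality Index and Berlin Questionnaire". It is absent from that legend's list of baseline-only forms.
- **Intervention.** Exercise Monitoring, for both arms: "Participants will be invited to perform exercise sessions at least 5 times a week". Remote Monitoring and Coaching adds a weekly call that motivates participants and collects their reported training.
- **Analysis.** Statistical Analysis says of the primary outcome that a significant difference "between pre- and post-intervention timepoints will be considered as the evidence of the intervention's efficacy", and then: "Secondary and exploratory outcomes will be analyzed as the primary outcome". The first hypothesis in the Introduction expects physical measures to improve after 6 months of exercise.
- **Design and dose.** Study Limitations states that there is no untreated arm. In partial compensation it plans to relate each participant's mean weekly exercise dose to cognitive and physical functions.
- **Disclosure.** Study Limitations also says that non-exercise prediction equations "could lead to a significant error in the estimated change" of fitness.

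**The concern.** An outcome meant to show that exercise improved fitness takes reported exercise as one of its inputs. Participants are asked to exercise more, are telephoned every week about it, and then answer a questionnaire whose activity answers feed the score. If they report more activity, the score can rise whether or not cardiorespiratory fitness has changed. Blinding the assessor does not help, because the input comes from the participant, and Blinding does not list participants among those kept unaware.

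At stake is a statement in the trial report that home-based exercise improved cardiorespiratory fitness, when the data may show only that people who were coached to exercise reported exercising more. The dose-response analysis is exposed in a second way: participants who report more exercise would tend to have a higher estimated VO2max partly because both quantities draw on their own account of their activity.

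**Working it through.** The point concerns how an outcome is built, so the plan has no figure for it to reproduce. The check sets out what can move the score, then gives an illustration on assumed values.

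**Step 1. Which inputs can move over 6 months.** Inputs from Secondary Outcome: Physical Functions:

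| Input | Possible within-person change, baseline to 6 months |
|---|---|
| Sex | none |
| Age | 0.5 year, nearly the same for everyone |
| Anthropometric data | possible; which measures, and their weights, are not given |
| Self-reported physical activity | possible; this is the behaviour the intervention targets |

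Writing the score as linear (an assumption, since the article gives no equation):

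change in score = b_age × 0.5 + b_anth × (change in anthropometry) + b_act × (change in reported activity)

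No term is an observed fitness measurement. Apart from the small common age term, change comes only from the last two terms.

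**Step 2. Pre/post contrast.** Split the change in reported activity into a true part T and a change in reporting error E. Suppose that true fitness responds to true activity by g × T, and set anthropometry aside. Then:

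score change − true fitness change = b_act × E + (b_act − g) × T

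Both terms depend on quantities the trial does not observe. No untreated arm shows what the score would do without the programme. A rise is therefore compatible with a real gain, with changed reporting, or with a mixture.

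**Step 3. Dose-response analysis.** Dose is computed from the activity journal, which Study Limitations describes as declarative only. Estimated VO2max uses activity reported on a separate questionnaire. The forms differ, but the same person reports the same behaviour on both, so part of any association is built in.

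**Step 4. Between-arm contrast.** Taking differences between arms:

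b_anth × (between-arm difference in anthropometric change) + b_act × (between-arm difference in change of reported activity)

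Both arms have the same exercise programme and the same weekly calls. A shift in reporting common to both arms cancels; distortion needs the arms to report differently.

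**Step 5. Illustration (assumed shifts, not from the document).** Sample Size Calculation gives 49 analysable participants per group, so 2 × 49 = 98 pooled. The figure of 49 reproduces: a difference of 0.186 with SD 0.325 at 80% power and two-sided 0.05 needs 48.9 per group by the noncentral t. Let true fitness be unchanged and let reporting alone raise the score by d standard deviations of change. With a normal approximation:

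P(significant rise) = Φ(d × √98 − 1.96), with √98 = 9.90

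| d | d × √98 − 1.96 | Probability |
|---|---|---|
| 0.1 | −0.97 | about 17% |
| 0.2 | 0.02 | about 51% |
| 0.3 | 1.01 | about 84% |
| 0.5 | 2.99 | over 99% |

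These figures show how sensitive a pooled pre/post test is to a modest reporting shift. They do not estimate the shift in this trial.

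**The case against.** **Already disclosed.** The article labels the measure as estimated or predicted throughout. Study Limitations says that little is known about the equation's reliability in cardiovascular disease, that such equations vary in detecting change, and that the estimated change may be seriously wrong. This stands as mitigation. It does not say that the targeted behaviour, as self-reported, is an input, and the outcome keeps its tier and its analysis.

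**The direction of bias is not established.** A reader might infer that the score is certain to be biased upward, that its change is almost entirely reported activity, or that it measures adherence and nothing else. The document does not support any of these. It gives no coefficients, does not say which anthropometric measures enter, and has no data on how much they change. If people truly exercise more and become fitter, a rise in the score is in the right direction, and step 2 shows that the sign of the error depends on unknown quantities. Adherence is tracked separately, by journal.

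**The efficacy sentence names only the primary outcome.** A reader might infer that a pre/post rise in estimated VO2max is formally declared to be efficacy. The sentence on secondary outcomes may carry over only the model. Even so, the first hypothesis expects physical measures to improve, so the pre/post change will be tested and interpreted.

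**The missing control affects every pre/post comparison.** This is true, and the four observed tests share the weakness. They do not share the self-reported input, which is the point here.

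**The randomised comparison is largely spared.** This stands in full. A reader should not infer that the added value of cognitive training is undermined.

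**Conclusion.** The point holds for the pre/post change in estimated VO2max and for its place in the dose-response analysis of physical functions. In both, an effect on fitness cannot be distinguished from a change in reported activity. The conclusion rests on the stated list of inputs, on the absence of an untreated arm, and on one assumption: that the equation predicts a higher VO2max when more activity is reported.

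The size cannot be derived from the document. The illustration runs from about 17% to over 99% for assumed shifts of 0.1 to 0.5 SD of change. One of five secondary physical measures is affected. The primary cognitive outcome, the sample size and the four observed tests are untouched, and the between-arm contrast is much less exposed. This is a worthwhile and inexpensive improvement, not a threat to the trial's main result.

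**What to change.** - Move change in estimated VO2max out of the secondary efficacy outcomes and report it as a descriptive or exploratory index derived from reported activity.
- Leave it out of the dose-response analysis of physical functions.
- Rest conclusions on physical function on balance, sit-to-stand, walking speed and Timed Up-and-Go.
- Add to Study Limitations that self-reported activity is an input to the estimate, so a change in it is not a measured change in fitness.

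The cost is one secondary claim: the trial would draw no efficacy conclusion on cardiorespiratory fitness. The questionnaire is still collected on the same schedule, and its baseline value can still describe the sample. The sample size and the primary analysis do not change.
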